### Sample size evaluation

This superiority study is designed to have a statistical power of 80% to detect a significant treatment effect on the first onset of pouchitis. We estimate a survival rate of 25% in the control group versus 60% in the treatment group at 6 months (hazard ratio = 0.3685).

These figures are based on the work on probiotics of Gionchetti and Mimura [18, 19].

A total of 32 events are needed to ensure a statistical power of 80%. For a 48-month enrollment period and 24-month follow-up period, 40 patients are needed to observe 32 events. To ensure this statistical power, a total of 42 patients will be randomized.

This sample size calculation takes into account the interim analysis planned at the first 16 observed events.

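### Under constant hazards, the sample-size inputs give about 37 to 39 events from 40 patients with 24 months of follow-up, not the stated 32

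*Protocol article*

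**What the plan says.** All the figures are in the section Sample size evaluation of the protocol article. The trial is "designed to have a statistical power of 80% to detect a significant treatment effect on the first onset of pouchitis". The effect assumption reads "We estimate a survival rate of 25% in the control group versus 60% in the treatment group at 6 months", and the article attaches "hazard ratio = 0.3685" to it. The event target follows: "A total of 32 events are needed to ensure a statistical power of 80"%. The conversion to patients is "For a 48-month enrollment period and 24-month follow-up period, 40 patients are needed to observe 32 events", and then "To ensure this statistical power, a total of 42 patients will be randomized". The section adds that the calculation allows for one interim analysis at the first 16 events.

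Three other places bear on the point. The patients section under Study population expects 5% loss to follow-up. The administration plan schedules visits up to 24 months. Statistical methods censors relapse-free patients at their last visit as of the time of the analysis, without saying what triggers that analysis.

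**The concern.** Thirty-two events from 40 patients means that 80% of patients relapse under observation. With only 25% of the control group expected to be relapse-free at 6 months, one would expect almost all controls to have relapsed by 24 months, and most FMT patients too. An overall 80% looks too low.

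The event count fixes both the power of the log-rank test and the information available at the interim look. If 40 patients and 24 months do not belong with 32 events, the stated size, follow-up and power describe more than one design, and a reader cannot tell which one will be run.

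**Working it through.** **Inputs** (Sample size evaluation unless noted): relapse-free at 6 months 25% sham and 60% FMT; power 80%; 32 events; 40 patients; 48 months of enrollment; 24 months of follow-up; 42 randomized; interim look at 16 events; 1:1 allocation (Randomization); 5% loss (Study population). Assumptions, because the article does not state them: two-sided alpha 0.05, constant hazards, uniform accrual.

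**1. Hazard ratio.** ln(0.60)/ln(0.25) = 0.3685. It reproduces.

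**2. Events.** Schoenfeld: 4(1.960 + 0.8416)² / (ln 0.3685)² = 31.5, rounded up to 32. It reproduces. One-sided 0.05 would give 25, so two-sided 0.05 is the reading that fits.

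**3. Patients, fixed 24 months each.** Twenty-four months is four 6-month periods.
- Sham: 1 − 0.25⁴ = 0.9961.
- FMT: 1 − 0.60⁴ = 0.8704.
- Mean: 0.933.
- Events from 40 patients: 37.3. Patients for 32 events: 32/0.933 = 34.3, so 35.

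**4. Patients, 48-month uniform accrual plus 24 months.** The monthly hazards are −ln(0.25)/6 = 0.2310 and −ln(0.60)/6 = 0.0851. The relapse probability is 1 − [exp(−24λ) − exp(−72λ)]/(48λ).
- Sham 0.9996, FMT 0.9688, mean 0.984.
- Events from 40 patients: 39.4. Patients for 32 events: 32.5, so 33.

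**5. Loss to follow-up.** With 5% loss a year as a competing dropout hazard, 40 patients give 36.4 events (fixed 24 months) or 38.2 (staggered accrual). With 5% over the whole 24 months, fixed, they give 36.9. Bringing 40 patients down to 32 events would take dropout of about 28% a year (fixed) or 32% a year (staggered).

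**6. What 42 patients deliver at a fixed 24 months.** Events: 42 × 0.933 = 39.2. Power: Φ(√39.2 × 0.998/2 − 1.960) = Φ(1.17) = 88%. The interim look is 16/32 = 50% of the information if the final analysis is at 32 events, and 16/39.2 = 41% if it waits for the end of follow-up.

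**7. Routes that arrive at or near 40.** None is stated in the article.
- *Another formula for N at 24 months.* Freedman: (1.960 + 0.8416)² × (1.3685/0.6315)² = 36.9 events, and 36.9/0.933 = 39.5, so 40 patients. Lachin–Foulkes gives 40.0 (fixed 24 months) or 39.3 (staggered). Under constant hazards these designs carry about 37 to 39 events, not 32.
- *Shorter effective follow-up.* Fixed 12 months: mean (0.9375 + 0.6400)/2 = 0.789, so 40 patients give 31.6 events and 32 events need 40.6, so 41. Accrual over 48 months with no added follow-up: mean 0.835, so 32 events need 38.3, so 39.
- *A declining hazard.* A Weibull model with shape 0.53 keeps the 6-month rates and the hazard ratio. At 24 months the cumulative hazard is 4^0.53 = 2.085 times that at 6 months. Relapsed: 1 − 0.25^2.085 = 0.944 and 1 − 0.60^2.085 = 0.655, mean 0.80, so 40 patients give 32.0 events at a fixed 24 months (about 35 with staggered accrual).

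**The case against.** The strongest objection is that constant hazards are not in the article. The stated hazard ratio needs only proportional hazards, and 24 months is four times the horizon at which survival is given. A hazard that declines over time can make the sentence true at a fixed 24 months, as the Weibull case shows. This stands as a limit on the point: the sentence fails under the usual constant-hazard model, not under every model. But the article does not mention a declining hazard, and the shape that works at a fixed 24 months no longer gives 32 under the staggered 48-month enrollment that the sentence names.

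A second objection is that a condensed article leaves formula, alpha, boundary and dropout model to the full protocol. That is fair, and their absence is not criticized here. The point concerns a relation between three numbers that the article does state.

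A third is that nothing is lost, since the discrepancy is conservative. That also stands, and it limits the weight of the point.

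Two stronger readings are tempting. A reader might infer that 40 was worked out for 12 months of follow-up, all the more because Table 5 has its last scheduled endoscopy at week 52 and only a clinical PDAI at week 104. The documents do not support this. Other routes also lead to 40 or close to it, and Table 5 includes PDAI, endoscopy and biopsies at unscheduled relapse visits, so a relapse after week 52 can be confirmed and counted. A 12-month basis would also need 41 patients (43 with 5% loss), so it would not restore the stated figures. A reader might also infer that the trial should shrink to 35 to 37 patients. That is a preference rather than a correction: it would remove the margin from a small trial whose effect size is borrowed from probiotic studies.

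**Conclusion.** The point holds in a limited form. Under constant hazards and two-sided alpha 0.05, the article's 6-month rates give about 37 to 39 events from 40 patients with 24 months of follow-up (about 36 to 38 with 5% yearly loss), and 32 events need about 33 to 35 patients. The stated 40 for 32 does not follow, and the article's 5% loss does not close the gap.

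The error runs in the safe direction. The 42 patients give about 88% power at a fixed 24 months. Even at 12 months each they would give 42 × 0.789 = 33.1 events and about 82% power. It should not be read as a loss of power.

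Where the mismatch comes from cannot be determined from the article. Schoenfeld events combined with an N from another formula, a shorter effective follow-up, and a non-constant hazard are all possible. The practical consequence is that the trigger for the final analysis, and with it the information fraction at the interim look, is left open between 50% and about 41%.

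**What to change.** Keep 42 patients and correct the sentence so that events, patients and follow-up agree. One wording that fits the recomputed figures: *With 24 months of follow-up, 42 patients are expected to yield about 39 events (about 88% power); 32 events suffice for 80% power.* Alternatively, keep the sentence and state the survival model and loss assumption under which 40 patients give 32 events.

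In either case, add one sentence saying whether the final analysis takes place at the 32nd event or at the end of follow-up, so that the look at 16 events has a defined information fraction.

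The cost is two or three sentences and no additional patients. The section Trial status reports that no patient had yet been included, so as of the article this can be settled before any data accrue.

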### Statistical methods

Individual disposition, demographics, and baseline characteristics will be summarized. Summary statistics for continuous variables will include the number of participants (n), mean, median, standard deviation or standard error, minimum, and maximum. For categorical variables, the frequency and percentage will be given.

It should be noted that if a participant is alive or lost to follow-up without experiencing documented relapse at the time of the analysis, the participant will be censored at the date of last visit.

#### Primary endpoint

The primary endpoint is the relapse delay. This is defined in weeks as the time from transplantation to the date of the clinical and endoscopic relapse. Relapse delay will be estimated using the Kaplan–Meier method. The comparison between treatment groups will be made using the log-rank test.

#### Secondary endpoint

Relapse rates at 24 weeks and 52 weeks will be reported for each treatment group. Delay within the transplantation and the instauration of an antibiotherapy or alternative treatment will be estimated using the Kaplan–Meier method. The comparison between treatment groups will be made using the log-rank test.

#### Disability

Total score on the IBD Disability Index will be estimated using a linear mixed model taking into account score at baseline (week 0), treatment, time (weeks 8 and 24), and treatment by time interaction.

#### Safety analyses

A list of AEs (whether severe or not) will be provided. Descriptive statistics, including the frequency of participants presenting at least one AE and the number of events, will be generated by severity and relationship to treatment. A review of the AEs occurring during the study period will be carried out.

No other additional analyses are planned.

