### Management of adverse events

Concerning the study treatment, the systematic review by Wang et al. (“Adverse Events of Fecal Microbiota Transplantation”) [24] will be used as the reference safety information. According to this review, the expected reactions for the lower gastrointestinal route are:
Gastrointestinal disorders: abdominal pain, abdominal fullness, constipation, bloating, abdominal cramp, diarrhea, nausea, transient relapse of pouchitis, irregularity of bowel movements, increase in stool frequency;Infections and infestations: bacteremia, multiorganism bacteremia, urinary tract infection, norovirus gastroenteritis;General disorders and administration site conditions: fever, chills;Investigations: temporary increase in C-reactive protein (CRP).

Most reactions reported are mild to moderate and concern abdominal pain, abdominal cramping, flatulence, increased stool frequency, constipation, fever, and a temporary increase in CRP.

An increasing intensity or frequency of these expected reactions will be viewed as unexpected. As recommended by ANSM, all medically significant infections will be treated as SUSARs (suspected unexpected serious adverse reactions [SARs]).

It has been suggested that some reactions—such as pouchitis flare, appendicitis, peripheral neuropathy, Sjogren’s disease, idiopathic thrombocytopenic purpura, and rheumatoid arthritis—might be related to FMT. In this trial, however, these events will not be viewed as expected reactions to FMT.

Any AR/AE, whether expected or unexpected, serious or not, will be recorded in real time in the study electronic case report form (eCRF).

All serious AEs/SARs must be reported to the trial’s sponsor if they occur to a research participant:
From the transplantation;As recommended by ANSM (the French regulatory authority), AEs (serious and not serious) must be recorded for 104 weeks after FMT, even if the patient leaves the study (early discontinuation);After the end of the patient follow-up period, and without any time limit if the investigator becomes aware of a SAR possibly linked to the experimental treatment.

In case of SAE, a code-break procedure of the pharmacovigilance unit will show immediately the status of the patient.

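### Pouchitis relapse, the primary efficacy event, also appears to count as an adverse event, so the pooled share of patients with any AE largely re-counts efficacy

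*Protocol article*

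**What the plan says.** All references are to the Protocol article.

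- **Safety analyses.** A list and a review of AEs are planned, and "Descriptive statistics, including the frequency of participants presenting at least one AE and the number of events, will be generated by severity"; the same sentence adds a breakdown by how the event relates to treatment. The section closes with "No other additional analyses are planned".
- **Management of adverse events.** Among reactions that might be related to FMT it names some "such as pouchitis flare, appendicitis, peripheral neuropathy, Sjogren’s disease, idiopathic thrombocytopenic purpura, and rheumatoid arthritis", and adds: "In this trial, however, these events will not be viewed as expected reactions to FMT". Its list of expected gastrointestinal reactions, however, includes "transient relapse of pouchitis, irregularity of bowel movements, increase in stool frequency". The recording rule is general: "Any AR/AE, whether expected or unexpected, serious or not, will be recorded in real time". Recording runs for 104 weeks, also after early discontinuation.
- **Table 5.** AE recording is scheduled at the unscheduled relapse visit as well as at the planned visits.
- **Endpoints.** The primary event is clinical and endoscopic relapse, PDAI of 7 or more.
- **Sample size evaluation.** "We estimate a survival rate of 25% in the control group versus 60% in the treatment group at 6 months", with 40 patients expected to yield 32 events.
- **Objectives.** Safety of FMT is a secondary objective.

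**The concern.** The efficacy event and the safety count are not separated. Relapse is handled as a reaction, every reaction is recorded, and no passage removes the primary-endpoint relapse from the AE count. The share of patients with any AE then consists mostly of patients who relapsed, and relapse is what FMT is meant to prevent.

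An effective FMT would lower this share through efficacy alone. A real excess of other adverse events could be offset or reversed in the one participant-level safety figure that the article names, and the article plans no summary that leaves relapses out.

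**Working it through.** **1. Inputs.** From Sample size evaluation: relapse-free at 6 months 25% (sham) and 60% (FMT), hazard ratio 0.3685, 32 events, 40 patients to observe them, 42 randomized (21 per arm). From Management of adverse events: a 104-week window, about 24 months. The article gives no rates for AEs other than relapse, so those used below are assumptions.

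**2. Reproducing the plan's figures.** HR = ln(0.60)/ln(0.25) = 0.3685. Schoenfeld's formula with two-sided alpha 0.05 (assumed; the article states none), 80% power and 1:1 allocation: 4 × (1.960 + 0.842)² / (ln 0.3685)² = 31.5, rounded up to 32. This matches.

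**3. Relapse within the AE window.**

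- *Constant hazard:* sham 1 − 0.25⁴ = 99.6%; FMT 1 − 0.60⁴ = 87.0%. In 40 patients that is 20 × (0.996 + 0.870) = 37.3 events, more than the 32 stated.
- *Stated event fraction, 32/40 = 80%, read as the average over both arms in this window:* solve s + s^0.3685 = 2 × 0.20 = 0.40, where s is the sham relapse-free share. This gives s = 0.0555, so 94.5% of sham patients relapse. The FMT relapse-free share is 0.3445, so 65.5% relapse.
- *Floor, no relapse after 6 months:* 75% and 40%, average 57.5%. This conflicts with the stated 80% and serves only as a stress test.

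**4. Effect on the pooled figure.** Let q be the share of patients with some other AE, independent of relapse. Then P(any AE) = 1 − (relapse-free share) × (1 − q). With q = 20% sham and 40% FMT:

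| Relapse assumption | Sham | FMT | FMT minus sham |
|---|---|---|---|
| Constant hazard | 1 − 0.0039 × 0.8 = 99.7% | 1 − 0.1296 × 0.6 = 92.2% | −7.5 points |
| 32/40 fraction | 1 − 0.0555 × 0.8 = 95.6% | 1 − 0.3445 × 0.6 = 79.3% | −16.3 points |
| 6-month floor | 1 − 0.25 × 0.8 = 80.0% | 1 − 0.60 × 0.6 = 64.0% | −16.0 points |
| Relapses left out | 20% | 40% | +20 points |

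The sign is reversed in all three relapse scenarios.

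**5. What 21 patients per arm would show.** With assumed other-AE rates of 30% sham and 60% FMT, the observed FMT share exceeds the sham share with probability 97% when relapses are left out. When they are counted, the probability is 2% (constant hazard), 7% (32/40 fraction) or 24% (floor).

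**6. Room left above sham.** The largest excess FMT could show is one minus the sham relapse share: 0.4 points under constant hazard and 5.5 points under the 32/40 fraction.

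**The case against.** - **Relapse as an AE is inferred.** No sentence says that each PDAI-defined relapse goes on an AE form, and the statement that flare is not viewed as expected governs how a reported case is classified. Relapse also has its own visit and PDAI record. This stands as a limit on certainty. The inference still rests on several statements that point the same way: flare and transient relapse named as reactions, a general recording rule, AE recording at the relapse visit, and no exemption.
- **An article condenses.** AE definitions may sit in the full protocol or the analysis plan, which are not shown. Here, though, the article itself fixes the summary and says that nothing further is planned.
- **Safety does not rest on one percentage.** Breakdowns by severity and relationship, a list and a review are also planned, the analysis is descriptive, and relapse is reported separately as efficacy. This stands: a specific FMT harm could show there. The breakdowns do not remove relapses, however. Since flare is named as possibly related to FMT, blinded investigators may attribute it to treatment in either arm.
- **Independence is doubtful.** The Background gives more bowel movements, abdominal pain and fever as features of pouchitis, and the same symptoms are listed as reactions. If all other AEs fell in patients who relapse, the pooled figure would simply equal the relapse rate. That is a purer re-count of efficacy, not a weaker one.
- **Leaving flares out would hide a suspected harm.** This stands, and is why both versions of the summary are needed.

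**Conclusion.** The point holds as a cheap improvement to a descriptive safety summary; the primary analysis is untouched. If relapses are logged as AEs, as the text most naturally implies, about 94.5% to 99.6% of sham and 65.5% to 87.0% of FMT patients enter the pooled figure through relapse alone. That figure can then favor FMT even when FMT causes more other AEs. The relapse range rests on the sample-size assumptions; the size of the reversal rests on assumed other-AE rates and on independence.

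A reader might infer three stronger things that the documents do not support:

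- *That the safety analysis cannot show FMT as less safe.* The breakdowns and the AE list could, and even the pooled figure leaves up to about 5.5 points under the 32/40 fraction.
- *That nearly every patient in both arms relapses.* This comes from extrapolating the 6-month rates, which overshoots the stated 32 events in 40. Under that fraction about a third of FMT patients stay relapse-free.
- *That relapses dominate the number of events.* They enter that count, but the article gives no event rates from which dominance could be shown.

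**What to change.** In Safety analyses:

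- Tabulate pouchitis relapses and flares on their own line, by arm.
- Report the share of patients with any AE and the number of events in two versions: with relapses, flares and the symptoms attributed to them, and without.
- Keep the severity and relationship breakdowns in both versions, and leave expedited reporting unchanged.

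In Management of adverse events:

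- State whether a PDAI-defined relapse is recorded as an AE.
- Reconcile the listing of transient pouchitis relapse as expected with the statement that pouchitis flare is not, so that centers code alike.

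The cost is one extra table row and a second version of the summary. Relapses are already identified for the primary endpoint; the only added step is to note which recorded symptoms are attributed to a relapse.

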### Management of adverse events

Concerning the study treatment, the systematic review by Wang et al. (“Adverse Events of Fecal Microbiota Transplantation”) [24] will be used as the reference safety information. According to this review, the expected reactions for the lower gastrointestinal route are:
Gastrointestinal disorders: abdominal pain, abdominal fullness, constipation, bloating, abdominal cramp, diarrhea, nausea, transient relapse of pouchitis, irregularity of bowel movements, increase in stool frequency;Infections and infestations: bacteremia, multiorganism bacteremia, urinary tract infection, norovirus gastroenteritis;General disorders and administration site conditions: fever, chills;Investigations: temporary increase in C-reactive protein (CRP).

Most reactions reported are mild to moderate and concern abdominal pain, abdominal cramping, flatulence, increased stool frequency, constipation, fever, and a temporary increase in CRP.

An increasing intensity or frequency of these expected reactions will be viewed as unexpected. As recommended by ANSM, all medically significant infections will be treated as SUSARs (suspected unexpected serious adverse reactions [SARs]).

It has been suggested that some reactions—such as pouchitis flare, appendicitis, peripheral neuropathy, Sjogren’s disease, idiopathic thrombocytopenic purpura, and rheumatoid arthritis—might be related to FMT. In this trial, however, these events will not be viewed as expected reactions to FMT.

Any AR/AE, whether expected or unexpected, serious or not, will be recorded in real time in the study electronic case report form (eCRF).

All serious AEs/SARs must be reported to the trial’s sponsor if they occur to a research participant:
From the transplantation;As recommended by ANSM (the French regulatory authority), AEs (serious and not serious) must be recorded for 104 weeks after FMT, even if the patient leaves the study (early discontinuation);After the end of the patient follow-up period, and without any time limit if the investigator becomes aware of a SAR possibly linked to the experimental treatment.

In case of SAE, a code-break procedure of the pharmacovigilance unit will show immediately the status of the patient.

### Ethical, regulatory, and dissemination aspects

The clinical study will be conducted in accordance with the relevant versions of the French Public Health Code, national and international good clinical practice (GCP) guidelines, and the Declaration of Helsinki, each in the applicable version.

The protocol was written according to a 33-item SPIRIT checklist [39] (see Additional file 1).

It has been possible to carry out the protocol and the trial thanks to an Executive Committee which includes a Scientific Committee and a Steering Committee, created and coordinated by [name]. The Steering Committee follows the development of the trial. It is composed of the members of the Scientific Committee with the addition of the data management team, the study coordinator from the Gastroenterology Department of CHU Nantes who coordinates assistance for patient inclusion in the other centers, and the monitoring Clinical Research Assistant (CRA).

In compliance with French law, the study protocol was submitted to the French regulatory authority (ANSM) and approved on June 8, 2018. It should be noted that in France, the pharmaceutical preparation status requires the preparation of feces for FMT to be carried out under the responsibility of the institution pharmacist. To do this, an application for authorization from a regional regulatory authority must be made. In our case, this authorization was given on May 25, 2018 by the Regional Health Agency of Pays de la Loire.

This clinical study and the donors’ and the patients’ written informed consent was submitted to and approved by the Ethical Review Board of Tours (Comité de Protection des Personnes de Tours, Région centre, Ouest-1) on June 26, 2018. Amendments, if necessary, will be sent to the ethical committee and regulatory authorities for approval. The updated protocol was at version 1.2 on June 8, 2018.

As required, the sponsor has provided an insurance policy to cover the financial consequences of its civil liability in accordance with the regulations.

All the submissions/declarations were made by the Sponsor Department of the University Hospital of Nantes.

The sponsor is responsible also for the quality of the trial data. Data collection for each person participating in the research is realized with an eCRF. The data will be stored directly from the eCRF into the database hosted on a dedicated server, with controlled access (account/password) according to the user role. Any addition, modification, or deletion of data will be recorded in a non-editable electronic file (the audit trail). The principal investigator and all co-investigators undertake to keep the identities of the persons who participate in the study confidential by assigning them a code.

This code will be used for all the eCRF and all the attached documents (reports of imaging exams, biology, etc.). It will be the only information which will make it possible to make the connection with the patient retrospectively.

The coding rule is the following: first letter of first name + first letter of surname +/– month and year of birth and the randomization number.

The data collected during the study will be processed electronically in accordance with the requirements of the CNIL, the French Data Protection Authority (in compliance with the French Reference Methodology MR001). The CNIL is an independent French administrative regulatory body whose mission is to ensure that data privacy law is applied to the collection, storage, and use of personal data.

An inspection or audit may take place as part of this study, performed by the sponsor and/or by the regulatory authorities. Inspectors will check the documents, logistics, records, and any other resources that the authorities consider to be associated with the clinical trial and that may be located at the trial site itself.

The trial results will be published in international gastroenterological, medical, and scientific journals and presented in national and international congresses. The datasets analyzed during the current study will be available from the corresponding author on reasonable request. The investigators, who will share only with each other the final trial dataset, will follow the rules and guidelines of the International Committee for Medical Journal Editors (ICMJE) [47]. The trial’s sponsor and the French Ministry of Health, who provided the grant, have to be cited in the publication.

